### Intervention Group Study Plan

After obtaining informed consent and baseline data, RA nurses provide health education through a booklet to patients and family caregivers and give them the booklet to follow the instructions at home. Subsequently, a video containing the risk factors of stroke and their management and prevention is shown to the patients and family caregivers. Health education sessions on booklet contents take around 20 minutes, and video show sessions take around 15 minutes. We provide these health education sessions 2 times after enrollment of the patients and 6 months after the follow-up visit in the hospital. Health education booklets guide patients on how to read food labels accurately for the prevention of stroke-related risk factors. Booklets have a reminder for the schedule date of the next clinic visits. There is also a notebook for recording daily health monitoring charts such as BP, exercise, and medication intake by the patients or caregivers. The video presentation includes simulation training on essential tasks such as how to measure BP and organize the medication boxes prescribed by physicians. We recommended placing the medications in our provided medication boxes to increase the adherence to doctors’ guidelines for consumption and using salt-measuring spoons. After that, an assigned physiotherapist provides about 15-minute exercise orientation sessions to show how to do physical exercises at home. A repeated session is conducted by the physicians and RA nurses at 6-month follow-ups for their memorization. RA nurses provide motivational SMS texts every month to the patients and caregivers to remind patients to measure their daily BP, reduce salt intake, avoid oily and fatty foods, consume more fruits and vegetables, exercise regularly, and adhere to their medication regimen. Additionally, RA nurses provide refresher health education twice a month in the first 3 months and then monthly in the next 9 months over a phone call to obtain information about the health condition of the patients and document in the questionnaires. Patients receive a reminder phone call on the fifth month to visit the hospital for the sixth month follow-up visit. At the 6-month follow-up visit (middle of study), if the patient and family caregiver are not able to come for any reason, RA nurses collect data and provide refresher health education over a phone call (Figure 3).

**Figure 3 figure3:**
[figure not shown]
Follow-up and evaluation timeline (months) of the intervention and control groups.

### Control Group Study Plan

The control group participants receive a monthly telephone call for 1 year from RA nurses solely to gather information about the patients’ health conditions and document the information in the questionnaires. At the fifth month, patients are reminded to visit the hospital for their sixth month follow-up visit (Figure 3). To mitigate the disadvantage faced by participants in the control group, after completing the study at the end point, they will be given the same health education booklet. If requested by the participants, a brief health education session will be provided based on the information contained in the booklet for their easy understanding.

### Outcomes and Data Collection Procedure

#### Primary Outcome

The primary end point is the recurrence rate of stroke at 12 months.

#### Secondary Outcomes

The secondary outcomes are (1) all adverse events (stroke and other events), (2) changes in the values of modifiable risk factors of BP, glycated hemoglobin, non–high-density lipoprotein cholesterol, and (3) changes in the scores of knowledge related to stroke in the investigator-developed questionnaire (this questionnaire consists of 10 items with “no/wrong answer,” “yes/correct answer,” and “don’t know” answers; the score ranges from 0 to 20, and a higher score indicates having better knowledge), (4) changes in scores in lifestyle behavior related to stroke in the investigator-developed questionnaire (this questionnaire consists of 14 items with a Likert scale to assess the frequency of behavioral changes; the score ranges from 0 to 37, and a higher score indicates having better lifestyle behavior), (5) changes in behavior in medication adherence by using Morisky Green Levine Medication Adherence Scale [34] (this questionnaire consists of 4 items with “yes=0” and “no=1” answers; the score ranges from 0 to 4, and a higher score indicates better compliance), and (6) changes in scores of QoL by using the QoL questionnaire (WHOQoL-BREF Bangla version [35]; each item scores from 1 [very poor or very dissatisfied] to 5 [very good or very satisfied] and ranges [mean of 2 items] from 1 to 5—a higher mean indicates a better QoL).

### Operational Definitions for This Study

#### Recurrence of Stroke

Recurrent stroke is defined as a new stroke event occurring at least 28 days after the stroke incident [32], which is confirmed by the physician who treats and diagnoses the patients in this study.

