
## Methods

### Study Design

This is an ongoing 12-month intervention study. This study follows a parallel (1:1), open-label, prospective, randomized controlled trial design, and adheres to the CONSORT (Consolidated Standards of Reporting Trials) guidelines [30]. The study flowchart is depicted in Figure 2. This study commenced in October 2022 and is expected to conclude in March 2024, with a total duration of 18 months. This trial is registered as ClinicalTrials.gov NCT05520034.

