#### Adverse Events

All adverse events (all causes of death, cardiovascular events) refer to all cases that need to be diagnosed, for example, recurrence of stroke, new onset of acute myocardial infarction and unstable angina, heart failure with hospitalization, and peripheral arterial disease with hospitalization—those that are confirmed by the physician who treats and diagnoses the patients in this study.

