#### Data Monitoring and Quality Assurance

The investigators (medical doctors) are directly involved in patient management. The investigators and the RA nurses have regular biweekly meetings for study purpose. Pretesting of the questionnaires was done among the patients (5% of the sample of 432) who did not participate in the main study. Additionally, for regular quality control purpose, investigators independently check 5% of the study participants’ data on the same day by using field testing. The investigators check the process of taking consent, data collection, and physical examination by the RA nurses. The detected errors are corrected immediately at the field site. For any query, RA nurses consult with the investigators. RA nurses fill up the questionnaires and enter the data into a password-protected computer. Investigators check the data and resolve the queries.

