### Strengths

We implemented various strategies to empower patients and caregivers, including training on BP measurement, medication box usage, salt intake measurement using spoons, and health education booklets. Self-monitoring of BP is facilitated by providing patients with a BP machine for daily measurements, which is generally not practiced in Bangladesh. Medication compliance is assessed using medication boxes, and accurate salt intake measurement will be facilitated by providing salt-measuring spoons. Most of the participants are not aware of the benefits of regular medication and low salt intake. Health education materials such as booklets and videos in Bengali are tailored to accommodate both literate and illiterate patients and their caregivers. Participants and even health care providers had no understanding to date about the advantage of health education in the health care system in Bangladesh. NINS&H is the only referral hospital in Bangladesh that patients attend from all over the country. Thus, our study findings can be generalized to all the patients who had a stroke in Bangladesh.

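### The primary end point is confirmed by the treating physician in an open-label trial, and the definition does not provide for strokes treated elsewhere or fatal at home

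*Protocol article*

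**What the plan says.** All references are to the protocol article.

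- **Recurrence of Stroke** (Operational Definitions): a recurrence is a new stroke at least 28 days after the first, "which is confirmed by the physician who treats and diagnoses the patients in this study".
- **Adverse Events**: the same clause covers all other events, including death from any cause: "those that are confirmed by the physician who treats and diagnoses the patients in this study".
- **Study Design**: "This study follows a parallel (1:1), open-label, prospective, randomized controlled trial design".
- **Data Monitoring and Quality Assurance**: "The investigators (medical doctors) are directly involved in patient management".
- **Strengths**: "NINS&H is the only referral hospital in Bangladesh that patients attend from all over the country".
- **Intervention Group Study Plan**: "RA nurses provide refresher health education twice a month in the first 3 months and then monthly in the next 9 months over a phone". If the 6-month visit is missed, "RA nurses collect data and provide refresher health education over a phone call".
- **Control Group Study Plan**: contact in this arm is set out as follows: "The control group participants receive a monthly telephone call for 1 year from RA nurses solely to gather information about the patients’ health conditions". No telephone substitute for a missed 6-month visit is described here.
- **Study Framework and Hypothesis**: the education covers recognising stroke symptoms and attending clinic regularly.
- **Background**: the first 3 months after a stroke are named as the period that matters most for recurrence.

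**The concern.** The trial asks whether recurrence over 12 months falls. What it counts is recurrence that a particular physician has confirmed. Two problems follow.

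The first is coverage. A patient who lives far from Dhaka may have a second stroke treated at a local hospital, or die of it at home. The definition does not say whether such an event counts or what evidence would confirm it.

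The second is masking. On the natural reading, the confirming physician is a study doctor who manages the patient and can know the arm. The research nurses who report health status by telephone also open the allocation envelopes and deliver the education.

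If capture is incomplete but equal, the trial loses power. If it differs by arm, the risk ratio itself is biased, and no analysis can recover events that were never counted.

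**Working it through.** **1. The plan's own figure.** Sample Size gives 10% v 20%, two-sided alpha 0.05, power 80%, with z values 1.96 and 0.84.

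n per arm = (0.10×0.90 + 0.20×0.80) × (1.96 + 0.84)² / 0.10² = 0.25 × 7.84 / 0.01 = 196.

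This matches the stated 196. Adding 10% gives 216 per arm, 432 in total, as stated. Power from a two-proportion z test (pooled variance under the null) is 79.4% at 196 per arm and 83.1% at 216. There is no arithmetic error.

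**2. Two readings of the confirmation clause.**

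| Reading | Strokes treated elsewhere or fatal at home | Masking |
|---|---|---|
| Study-hospital physician | No stated route to confirmation | The treating doctors in an open-label trial confirm |
| Any physician treating the participant | Outside hospital diagnoses count, by local criteria; a death at home without a physician is still not covered | No masked step stated |

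Neither reading settles the matter.

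**3. Planned contact.** Intervention: 2 × 3 + 1 × 9 = 15 calls. Control: 1 × 12 = 12 calls. The excess of 3 lies wholly in the first 3 months (6 v 3). The hospital-based Bangladeshi study cited in Background reports 14.7% recurrence at 3 months and 20% at 1 year, so 14.7/20 = 73.5% of its first-year recurrences came in that period. Some of these may fall inside the 28-day window that this trial excludes; the documents do not say how many.

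**4. Effect of incomplete capture.** The documents give no capture share, so every share below is an assumption. Counted rate = true rate × capture share, at 196 per arm.

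Equal capture in both arms (risk ratio stays 0.50):

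| Captured | Counted rates | Power |
|---|---|---|
| 100% | 10% v 20% | 79.4% |
| 90% | 9% v 18% | 74.3% |
| 80% | 8% v 16% | 68.5% |
| 70% | 7% v 14% | 61.9% |
| 50% | 5% v 10% | 46.8% |

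Unequal capture (intervention / control), true rates 10% v 20%:

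| Captured | Counted rates | Risk ratio | Power |
|---|---|---|---|
| 90% / 70% | 9% v 14% | 0.09/0.14 = 0.64 | 34.1% |
| 70% / 90% | 7% v 18% | 0.07/0.18 = 0.39 | 91.2% |

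Worked case, 9% v 14%: pooled rate 0.115; SE under the null = √(2×0.115×0.885/196) = 0.0322; SE under the alternative = √((0.09×0.91 + 0.14×0.86)/196) = 0.0321; power = Φ((0.05 − 1.96×0.0322)/0.0321) = Φ(−0.41) = 34%.

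No true effect (20% in both arms): the same shares give 18% v 14%, or the reverse. The two-sided rejection rate is 19.0% in place of 5%. The first pattern would look like harm, the second like benefit.

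**5. Expected workload.** 216×0.10 + 216×0.20 = 21.6 + 43.2 = 64.8, about 65 recurrences at the planned rates.

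**The case against.** A reader might infer that strokes treated elsewhere or fatal at home drop out of the primary end point. The documents do not support that. The clause can mean any physician who treats the participant. Even on the narrower reading, confirming is not witnessing: nothing bars a study physician from confirming an outside stroke from records or a caregiver's report. Both arms are phoned at least monthly, are assessed at 6 and 12 months, and the investigators and nurses meet every two weeks, so outside events can come to light. A death at home has a place among the adverse events, though under the same confirmation clause and not as a primary event.

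The article is also a condensed text. The full protocol may describe record retrieval and adjudication, and their absence here is not the point.

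Finally, the capture shares are assumed. The 20% control rate comes from a hospital-based study that may itself have missed outside events, in which case discounting it would count the loss twice. The documents cannot settle this.

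All of this stands, and it limits the claim to events that may be missed. It does not cure the definition. Detection by telephone is not confirmation, and the article states a confirmation rule that names the treating physician without saying what evidence suffices.

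**Conclusion.** The point holds as a badly fixed definition of the primary end point, not as proof that events are lost. Confirmation is tied to the treating physician in an open-label trial, and the rule makes no provision for strokes treated at other hospitals or fatal at home, despite the national catchment. Unequal capture is plausible because symptom teaching, encouragement to attend and the extra early calls all fall in one arm.

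Neither the size nor the direction of any bias can be read from the documents. It would be wrong to conclude that the rule must hide a benefit: better capture in intervention would, but knowledge of arm at confirmation could favour either arm. Under the assumed 90%/70% split, a true risk ratio of 0.50 could read anywhere from 0.39 to 0.64 depending on which arm loses more, and the false-positive rate could reach about 19%. The sample-size calculation is unaffected.

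**What to change.** 1. Reword both definitions (Recurrence of Stroke and Adverse Events) so that a recurrence counts if documented by any hospital, by discharge note or brain imaging, and a death counts as a fatal recurrence if records or a structured caregiver account support it.
2. Ask the same event questions at the same monthly time points in both arms, and obtain copies of records through those calls. The extra early intervention calls should not serve as additional event checks. Relying on the call schedule as it stands would leave the 15 v 12 imbalance in place.
3. Have an existing study physician who is not treating the patient classify each suspected event from a summary with arm and education notes removed.
4. Report events confirmed at the study hospital as a sensitivity analysis.

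Enrolment is complete and follow-up is described as under way, so the reworded rule should be fixed before events are classified for analysis. Months already passed would need a retrospective question, identical in both arms.

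**Cost.** Modest record retrieval, redaction and classification for about 65 or more suspected events. It depends on a non-treating physician being available, which the article does not state. Diagnosis will be less certain for some outside or home events, which the sensitivity analysis would show.

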#### Adverse Events

All adverse events (all causes of death, cardiovascular events) refer to all cases that need to be diagnosed, for example, recurrence of stroke, new onset of acute myocardial infarction and unstable angina, heart failure with hospitalization, and peripheral arterial disease with hospitalization—those that are confirmed by the physician who treats and diagnoses the patients in this study.

#### Sample Size

Stroke recurrence rate in Bangladesh was 20% within 1 year in 2019 [8]. A study that evaluated the effectiveness of health education in preventing the recurrence of stroke showed 50% reduction among the intervention group compared to the control group [13]. The expected proportion of outcomes from the intervention group was assumed as P1=0.10; P2 (proportion of outcome from control group)=0.20; α=.05 (2-tailed), 1-β=.80; Z1-α/2=Z, α=1.96; and Z1-β=Z, β=.84. We found that the estimated sample size was 196 for each arm (a total 392 for both arms). By considering 10% dropout, the total sample size was 432 (216 for each arm).

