### Statistical Analysis

To compare the outcomes of the intervention group and the control group, we will conduct an intention-to-treat analysis and a full set analysis. A chi-square test will be performed for categorical data, and a 2-sided *t* test or Mann-Whitney *U* test will be employed for continuous variables, as appropriate, to compare the 2 groups. For the primary end point, the cumulative risk of recurrence and adverse events occurring in 12 months will be estimated using the Kaplan-Meier method and presented overall by age group and by stroke subtypes. For the secondary end points, an analysis of covariance will be conducted to assess the effect of the intervention on the outcomes by adjusting confounding variables. Changes in outcomes over time will be analyzed using repeated-measures analysis of variance as well as regression analysis. Friedman test will be performed to examine the changes within the groups. Associations between risk factors and outcomes will be tested using Cox proportional hazards models, adjusting for all baseline factors. Additionally, laboratory test and physical examination data will be analyzed using 2-sided *t* tests or 2-way repeated-measures analysis of variance, considering data normality. For the knowledge-related questionnaire, medication adherence–related questionnaire, and QoL, reliability checking will be performed, and total scores will be calculated. The significance level will be set at .05. Data analysis will be conducted using SPSS (version 26.0; IBM Corp).

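### The 10% dropout allowance is about two patients per arm short: 216 per arm less 10% leaves about 194, just under the 196 the protocol says it needs

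*Protocol article*

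**What the plan says.** The Sample Size section sets out its inputs. For the intervention arm: "The expected proportion of outcomes from the intervention group was assumed as P1=0.10". For the control arm: "P2 (proportion of outcome from control group)=0.20". The significance level is .05, two-tailed, with 80% power, and the normal quantiles are printed as "Z1-α/2=Z, α=1.96; and Z1-β=Z, β=.84". Allocation is 1:1 (Study Design).

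The result before dropout is given as "We found that the estimated sample size was 196 for each arm", 392 in total. The allowance for loss follows: "By considering 10% dropout, the total sample size was 432 (216 for each arm". No inflation formula is shown.

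The Patient Enrollment and Results sections report that 216 patients were allocated to each arm and that enrolment is complete.

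**The concern.** A dropout allowance is there so that the required number remains after the expected loss. The number to randomise, reduced by 10%, should therefore give back at least 196 per arm. It gives 194.4. Two figures in adjacent sentences of the Sample Size section therefore do not fit together.

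At stake is whether the stated 80% power survives the protocol's own dropout assumption. The sample size statement is also likely to be repeated in the results paper, where a reader can check it in one line.

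**Working it through.** **Inputs, all from the Sample Size section:** intervention 0.10, control 0.20, z values 1.96 and 0.84, dropout 10%, 196 per arm before dropout and 216 after.

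**1. Reproduce the 196.** The two-proportion formula with separate (unpooled) variances is

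n = (z₁ + z₂)² × [p₁(1 − p₁) + p₂(1 − p₂)] / (p₁ − p₂)²

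= (1.96 + 0.84)² × (0.09 + 0.16) / 0.01 = 7.84 × 25 = 196.0.

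This matches the stated figure exactly.

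**2. Reproduce the 216.**

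| Rule | Per arm | Total |
|---|---|---|
| Multiply by 1.10 | 196 × 1.10 = 215.6, so 216 | 392 × 1.10 = 431.2, so 432 |
| Divide by 0.90 | 196 / 0.90 = 217.8, so 218 | 392 / 0.90 = 435.6, so 436 |

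The stated 216 and 432 match the first rule and not the second.

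**3. What remains after a 10% loss.**

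- From 216 per arm: 216 × 0.90 = 194.4. In total, 432 × 0.90 = 388.8, against 392.
- From 218 per arm: 218 × 0.90 = 196.2, which meets the target.

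The shortfall in numbers randomised is 2 per arm, 4 in total.

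**4. Effect on power, by the protocol's own formula.** Power = Φ(0.10 / √(0.25 / n) − 1.96).

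| Complete per arm | 0.10 / √(0.25 / n) | Power |
|---|---|---|
| 194 | 2.786 | 79.6% |
| 196 | 2.800 | 80.0% |
| 216 (no loss) | 2.939 | 83.6% |

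The loss is about 0.4 percentage points.

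**5. If patients lost partway are censored.** A patient who leaves at month 8 still contributes eight months. For 216 randomised to be worth fewer than 196, each dropout would have to lose about 93% of his or her information: (1 − 196/216) / 0.10 = 0.926.

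Two illustrations follow. Both assume dropout spread evenly over the 12 months, which the protocol does not state.

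- *Constant event rate.* A dropout loses about half of the information: 216 × (1 − 0.10 × 0.5) = 205.2 per arm.
- *Early-weighted recurrence,* as in the Bangladeshi hospital study cited in the Introduction (14.7%, 15.3%, 17.3% and 20% at 3, 6, 9 and 12 months). With straight lines between these points, starting from zero, the mean of the curve over the year is (7.35 + 15.0 + 16.3 + 18.65) / 4 = 14.3. As a share of 20 this is 72%, so a dropout loses about 28%: 216 × (1 − 0.10 × 0.28) = 210 per arm.

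Both exceed 196. The second depends on a curve that may not carry over, because the protocol counts a recurrence only from day 28 (Recurrence of Stroke).

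**The case against.** The strongest reply is that nothing turns on this. The inputs are round planning values, the gap is two patients per arm, and enrolment has closed. The Statistical Analysis section commits to intention-to-treat, names Kaplan-Meier estimation for the primary end point and plans Cox models, so patients lost partway would be censored and not deleted. On that view 194 is a worst case, and 216 may well be enough. All of this stands, and it sets the size of the point. It does not remove the point: the sample size was worked out by comparing two proportions, and on that basis 216 less 10% is not 196. It is also fair to say that multiplication by 1.10 is inferred. However 216 was reached, it leaves 194.4.

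A reader might go further and infer that the planned test needs more than 196 per arm. The Statistical Analysis section does say "A chi-square test will be performed for categorical data", and a pooled-variance formula would give 199 per arm. The document does not support that as a fault. The sentence is generic, and the sentence about the primary end point names Kaplan-Meier. The unpooled formula is standard and reproduces 196 exactly. A reader might likewise assume a continuity correction and arrive at clearly lower power, but the article nowhere mentions one.

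**Conclusion.** The point holds as a minor arithmetic slip. The stated 216 per arm does not preserve the stated 196 under the stated 10% dropout; 218 per arm (436 in total) would have. The cost is about 0.4 points of power, 79.6% against 80.0%, on three assumptions: 10% against 20% recurrence, two-sided .05, and dropouts contributing nothing. If they are censored at the time of loss, the cost is less and may vanish.

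A reader might infer that the trial is materially underpowered. The figures do not show that: the design loses less than half a percentage point in the worst case considered here. The slip gives no reason to enrol more patients, to change the sample size formula or to choose a different test.

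**What to change.** Restate the dropout sentence in the Sample Size section, and carry the same wording into the results paper: 432 patients randomised (216 per arm); if 10% drop out, about 194 per arm with complete 12-month follow-up; power about 79.6% for 10% against 20% at two-sided .05. If wanted, add that patients lost partway are censored in the Kaplan-Meier and Cox analyses, so that this is a lower figure.

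The cost is one sentence. No further enrolment and no change to the analysis are needed. The stated power becomes slightly less favourable.
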